### Eligibility criteria

Eligible participants will comprise adolescent mothers aged 10–19 years who:Have at least one biological child aged 1–3 years.Can speak and understand the main language used in the mothers’ clubs in the study context.Have been resident in the study site for at least 1 year.Consent/assent to being in the study (and, for minors, whose parents/guardians provide consent).

Adolescent mothers who are living with disability will be eligible to participate as long as they meet the eligibility criteria.

### Exclusion criteria

Currently pregnant.Unable to participate in the adolescent mothers’ clubs.

### Randomization and data collection

In each site, adolescents mothers will be interviewed at baseline and endline using a structured questionnaire drawn from the ‘*Understanding the lived experiences of pregnant and parenting adolescents in Burkina Faso and Malawi*’ study [4, 19]. The questionnaire includes questions on adolescent mothers’ sociodemographic and background characteristics, including their schooling and desire to return to school; family characteristics; social capital and networks; self-reported physical and mental health; marriage and sexual behavior; SRH knowledge and contraceptive behavior; pregnancies and births; HIV/AIDS and other sexually transmitted infections; gender-based violence and adverse childhood experiences; aspirations, concerns and perceived life chances; and self-efficacy.

At the end of the baseline survey, adolescent mothers will be individually randomly assigned to one of the three intervention groups using computer generated random numbers. CHWs facilitating the adolescent mothers’ clubs will be blinded to the adolescent mothers’ study arm.

### Process evaluation

Between the baseline and follow-up survey, we will conduct a process evaluation. The process evaluation will seek to: understand adolescent mothers’ and other key stakeholders’ perceptions of the interventions including barriers and facilitators in taking up the interventions assess the feasibility of delivering the three interventions in the study contexts; and assess the uptake of the three interventions.

#### Targeted population and approach

The process evaluation will use quantitative and qualitative approaches. The qualitative approach will include observations of the adolescent mothers’ clubs, repeated in-depth interviews (IDIs) with 21 of the adolescent mothers to understand their experiences with the interventions as well as the barriers and facilitators to (re)enrolling in school or vocational training and in accessing childcare services. In addition, key informant interviews will also be conducted with heads of schools/vocational training centers where these adolescent mothers are enrolled, managers of the child care centers where the children of the adolescent mothers are enrolled and parents/partners of the adolescent mothers participating in this program. In addition, we will also observe some activities of the intervention, including the mothers’ clubs and day-care visits to capture the dynamics in such spaces, the information provided to adolescent mothers and how they relate to the information, while documenting their effective presence and that of their child.

For the IDIs, we will purposively select 21 adolescent mothers. These adolescents will be selected from the three intervention arms: seven per arm. To capture a diversity of experiences, we will aim to have a sample comprising adolescent mothers of different ages, religion, schooling status, occupation, living arrangements and marital status, as well as from different areas of residence. Upon selection, we will conduct an initial IDI using a semi structured guide to document their living conditions as parenting adolescents, including challenges experienced, relations with their relatives and partners, reasons for dropping out of school, stigma, adolescent mothers’ knowledge on parenting and the type of support they receive from relatives, reproductive and mental health issues, among other issues. We will then conduct follow up interviews every 3 months to document changes in their living conditions, including their experiences with the interventions as well as the barriers and facilitators to (re) enrolling and remaining in school or vocation training and in accessing childcare and other services. The initial interview will be used as the basis for questions for the follow-up interviews. The interviews will take place at home or a venue suitable for the adolescent mothers.

We will also interview key actors involved in adolescent mothers’ lives such as head teachers in schools where these adolescent mothers are enrolled, managers of the childcare center where the children of the adolescent mothers are enrolled, as well as parents and partners of the adolescent mothers participating in this program. These interviews will aim at capturing their perspectives about the program, its impact on their practices and behaviors towards adolescent mothers.

In addition to individual level observations, we will also follow up the adolescent mothers as they engage with some activities of the intervention, including the mothers’ clubs and day-care visits to capture the dynamics in such spaces, the information provided to adolescent mothers and how they relate to the information, while documenting their effective presence and that of their child. The research team will document observations using field notes.

The qualitative data will be complemented by administrative data on the costs of implementing the interventions, attendance in the adolescent mothers’ clubs, use of childcare centers, as well as adolescent mothers’ enrolment in school and vocational training. This data will be gathered from the financial reports, as well as the day-care and school registries.

### Cost-effectiveness evaluation

The cost-effectiveness evaluations will examine the value for money of the three interventions in promoting adolescent mothers’ (re)entry and enrolment into school or vocational training, and document the additional value of the proposed interventions on SRH and mental health outcomes. The cost-effectiveness analysis will be carried out from the government-funded program perspective. The costing assessment will focus on the total costs that would be incurred by the government in delivering the integrated interventions. More specifically, we will assess the annual incremental costs of the delivery of each intervention including start-up and implementation costs.

The start-up costs will capture all the costs incurred for the preparation and introduction of the interventions while the implementation costs will consist of the costs incurred for the implementation of the intervention activities. These include incurred costs for the identification and hiring of program staff, identification of childcare centers to be involved in the intervention, development of the system for administering and monitoring the childcare voucher system, setting up of the cash transfer system, inception meetings including CHWs, initial training, cost associated with mentoring CHWs as they deliver the interventions, costs for sensitization and awareness-raising activities, supervision/monitoring during start-up as well as cost associated with overall coordinating activities and capital items acquired in the start-up. The start-up costs will be annualized accordingly.

The implementation costs will encompass all relevant costs such as the costs for mentoring and supervision, replenishment of capital items, mothers’ club operation costs, printing and materials, vouchers paid to childcare centers, amounts transferred in cash to adolescent mothers, and time invested by CHWs in facilitating the adolescent mothers’ clubs.

#### Data sources

To estimate these costs, we will use both primary and secondary data. Primary data will be obtained by collecting self-reported estimates of time use data from CHWs delivering adolescent mothers’ clubs. Secondary data will be collected by capturing the costs associated with launching and rolling out the interventions. The former costs include salaries and stipends (for CHWs), mobilization and sensitization, training, material, transport (including for mentoring and monitoring purposes), mentorship and supervision, and per diems, and will be determined by analyzing implementers’ financial documents as well as budgets.

### Data processing and analysis

Outcomes will be measured pre-randomization (at baseline) and at the end of the 12-month intervention period (endline). Quantitative data will be collected on Android-based tablets programmed using SurveyCTO. The data will be synchronized to a password protected server. The data will then be transferred to Stata for further cleaning and analyses.

At the endline, we will estimate the average treatment effect across the three groups using intent-to-treat (ITT) analysis, comparing school/vocational training enrolment at baseline and endline. Primary analyses will be unadjusted. We will also compute adjusted effects (controlling for covariates) to account for differential attrition or any differences at baseline. Drawing on financial records detailing the cost of the interventions (cash transfers, childcare vouchers, and cost of running the mothers’ clubs), we will conduct cost-effectiveness analyses of the interventions. The cost per (re)enrolled adolescent mother will be the primary measure of the cost-effectiveness of the interventions. This costing data per adolescent mother will be further combined with secondary effectiveness data to calculate additional cost-effectiveness estimates of the interventions. Secondary effectiveness data will be measured through improvements in mental health of adolescent mothers and improved knowledge and uptake of SRH practices.

All recorded qualitative interviews undertaken for the process evaluation will be translated and transcribed into English by bilingual transcribers. The interviews from Burkina Faso will be initially transcribed directly in French from local languages. The transcripts and field notes will then be translated into English in order to obtain bilingual transcripts. To ensure the accuracy of transcription, we will compare the transcripts of a selected number of interviews with the original recordings. The transcripts and field notes will be imported into NVivo (or other software) for data coding. Two researchers will independently code the data. We will develop a codebook using both inductive and deductive approaches, that is, using the study objectives as the starting point but also expanding as we read and re-read the transcripts. Before coding the transcripts, transcripts will first be read for familiarity and then followed by a more reflexive and critical reading. At this stage, data will be grouped into issues that are directly related to the study objectives. Once the coding is completed, we will compare the codes generated by the two researchers and group the final codes to themes. Using thematic analysis and the field notes, we will ensure that all relevant information is coded and grouped into themes. We will explore each theme to create subthemes. Our themes will be discussed with both research teams to ensure they accurately capture respondents’ narratives. An experienced qualitative researcher will analyze a random sample of our data and field notes to ensure the credibility of our analysis. We will ensure that views, both supportive of or against our thesis, are accurately reflected in our analysis. Verbatim quotes will be used to support emerging themes from our qualitative findings.

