### Outcomes

#### Primary outcome

The primary outcome of this study is (re)entry or (re)enrolment in school or vocational training. At baseline, all participants will respond to a question on current school and vocational training enrolment and their intention to return to school or vocational training. At endline, participants will be asked whether they have attended school or vocation training at any time after the baseline. The primary outcome will be a binary variable coded 1 “Yes” or 0 “No” indicating whether or not the participant was enrolled in school or vocation training during the 12-month long intervention period.

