### Covariates

The following covariates will be considered in comparing intervention effectiveness outcomes between the intervention arms: age, socio-economic status, family structure, family support, marital status, living arrangements, employment status, and neighborhood safety nets and assets.

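### The unadjusted primary analysis and the covariate list both leave out baseline enrolment, which gives up precision that the data already collected could supply

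*Protocol article*

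**What the plan says.** All references are to the protocol article.

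- **Data processing and analysis.** The intention-to-treat comparison is described as "comparing school/vocational training enrolment at baseline and endline". The next sentence reads "Primary analyses will be unadjusted", and the one after it "We will also compute adjusted effects (controlling for covariates) to account for differential attrition or any differences at baseline".
- **Covariates.** Eight items are listed: "age, socio-economic status, family structure, family support, marital status, living arrangements, employment status, and neighborhood safety nets and assets". Baseline enrolment is not among them. Neither are intention to return and site.
- **Primary outcome.** "At baseline, all participants will respond to a question on current school and vocational training enrolment and their intention to return to school" (the intention question covers training as well). The outcome is binary and records "whether or not the participant was enrolled in school or vocation training during the 12-month long intervention period".
- **Eligibility and exclusion criteria.** No criterion removes mothers who are already in school or training. The two exclusions are current pregnancy and being unable to take part in the clubs.
- **Randomization and data collection.** Allocation is individual and follows the baseline survey, so the baseline answers are pre-randomisation values.

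**The concern.** Because already-enrolled mothers may join and any enrolment in the 12 months counts as a success, a mother in school at baseline will almost always score 1 whichever arm she is in. These mothers add outcome variance that has nothing to do with treatment. A chance imbalance in their number between arms passes nearly one for one into the unadjusted estimate. The adjusted analysis is meant to deal with baseline differences, yet its list omits the baseline value of the outcome itself.

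Precision matters here because, under Sample size and sample selection, the pilot is meant to supply an effect-size estimate for a larger trial.

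The text is also unclear about what baseline enrolment is for. A comparison of enrolment at baseline with enrolment at endline does not fit an unadjusted analysis of an outcome defined only on the follow-up period.

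**Working it through.** **1. The plan's own figure.** Inputs from Sample size and sample selection: 94% out of school with clubs only, a 15-point reduction (so 79%), two-sided 10% level, 80% power, design effect 1.1, 15% loss. The printed formula gives 63.1 per arm. Then 63.1 × 1.1 / 0.85 = 81.7; rounding up at each step gives at most 84. The stated 90 is not reproduced, but it is larger, so it errs on the safe side. With 90 enrolled, 90 × 0.85 / 1.1 = 69.5 effective per arm, and power is 0.83. That calculation makes no use of baseline covariates.

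**2. Inputs for the effect of adjusting.**
- Baseline enrolment b: 18% in Ouagadougou and 6% in Blantyre, from 82% and 94% out of school under Study sites.
- Re-entry among the non-enrolled: 6% versus 21%. This is an assumption that carries the plan's 15-point difference over to that group.
- Share q of baseline enrolees scored 1: 100% first, then 70–90% (assumption).
- Analysed per arm per site: 90 × 0.85 = 76.5. The design effect is ignored; it would inflate both variances alike and leave the percentage cut unchanged.

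**3. Formulas.** With arm rate r = bq + (1 − b)p:
- unadjusted variance × n: r₀(1 − r₀) + r₁(1 − r₁)
- adjusted variance × n: (1 − b)[p₀(1 − p₀) + p₁(1 − p₁)] + 2bq(1 − q)

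The second averages the within-stratum variances. It drops a small term for the effect differing between strata, worth less than half a percentage point of the cut.

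**4. All enrolees scored 1.** Here p₀(1 − p₀) + p₁(1 − p₁) = 0.06 × 0.94 + 0.21 × 0.79 = 0.2223.

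| | Ouagadougou | Blantyre |
|---|---|---|
| Arm rates | 22.9% v 35.2% | 11.6% v 25.7% |
| Unadjusted variance × n | 0.4048 | 0.2940 |
| Adjusted variance × n | 0.82 × 0.2223 = 0.1823 | 0.94 × 0.2223 = 0.2090 |
| SD of risk difference | 0.073 to 0.049 | 0.062 to 0.052 |
| Variance cut | 55% | 29% |
| Power, two-sided 10% | 0.52 to 0.81 | 0.74 to 0.85 |

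A separate simulation of the same set-up with a linear model and robust standard errors gave cuts of 52% and 28%.

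**5. Weaker links.**
- If 70–90% of enrolees score 1, the cut is 27–45% in Ouagadougou and 14–23% in Blantyre.
- If Ouagadougou enrolment is 9%, half the survey figure, the cut is 18–38% over q from 70% to 100%.
- One-site simulations at 6% enrolment and 70 effective per arm, adjusting for baseline enrolment and intention, used assumed odds ratios of 5 and 2, 20 and 3, and 50 and 5. The cuts were 2%, 13% and 19%.
- If baseline enrolees are excluded, the variable is constant and gives nothing. Site plus intention then saves about 2–4%, even assuming that intention triples re-entry.

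**6. Chance imbalance.** Between two arms of 90 in Ouagadougou, the SD of the difference in baseline enrolment is √(2 × 0.18 × 0.82 / 90) = 0.057, or 5.7 points against a 15-point target.

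**7. Bias.** In the simulations the unadjusted risk difference averaged 0.149–0.151 against a true 0.15.

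**The case against.** The strongest reply is that nothing here is invalid. Under individual randomisation the unadjusted comparison is unbiased, its interval already allows for chance imbalance, and it matches the unadjusted formula used for the sample size. Adjusted effects are planned alongside. All of that stands, and a reader who inferred bias or an invalid analysis would be wrong.

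Second, the article does mention baseline enrolment in the intention-to-treat sentence. If that means a difference in changes, much of the loss disappears. With every enrolee scored 1 in Ouagadougou, the change-score variance × n is 0.0492 × 0.9508 + 0.1722 × 0.8278 = 0.1893, close to the adjusted 0.1823. At q = 70% it saves only 11%, against 27% for adjustment. But that reading contradicts the word unadjusted, and it sets current enrolment at baseline against any enrolment over 12 months. The text does not settle it.

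Third, the large savings depend on how already-enrolled mothers are counted. The objectives speak of re-entry, and if these mothers were excluded the gain would nearly vanish. This stands and limits the claim. The power figures in step 4 are also not the plan's: placing enrolees on top of the assumed re-entry rates shrinks the Ouagadougou difference to 0.82 × 15 = 12.3 points. The survey rates include pregnant adolescents, whom the trial excludes.

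Three stronger readings are tempting and not supported:
- **That all three omitted variables are the strongest predictors.** The documents give no association for any of them. Only baseline enrolment is prognostic by the outcome's coding.
- **That site must be adjusted for.** The 270 are per site and pooling is not stated; within one site it is a constant. The 39% and 76% wishing to return are not comparable either, since the Malawi figure is conditional on financial and childcare support.
- **That allocation should have been stratified.** An article may leave strata and blocks to the full protocol.

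**Conclusion.** The point holds as a loss of precision, not as an error. The article positively chooses an unadjusted primary analysis and prints a covariate list without the baseline value of the outcome, although that value is available for everyone and is strongly prognostic under the stated coding and eligibility.

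The variance saving is up to about 50–55% in Ouagadougou and 28–29% in Blantyre if the earlier survey rates apply, re-entry is 6% versus 21% among the non-enrolled, and every baseline enrolee scores 1. These are upper figures. Weaker links give less, down to a few per cent, and exclusion of enrolees leaves almost nothing to gain. The unclear role of baseline enrolment in the intention-to-treat sentence needs settling whatever the size of the gain.

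**What to change.** 1. Under Data processing and analysis, make the primary estimate the risk difference adjusted for baseline enrolment, and for site if the sites are pooled. A linear model or a standardised logistic model with robust standard errors would serve. Report the unadjusted estimate as supportive.
2. Under Covariates, add baseline school or vocational enrolment and, optionally, intention to return.
3. Reconcile the sentence on comparing baseline with endline enrolment with the choice of primary analysis and with the outcome definition, stating exactly how baseline enrolment enters.

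All the variables are already collected, so the cost is analysis wording only. The changes should be made before endline data are seen.

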### Sample size and sample selection

Aside from using the pilot study to assess the feasibility and implementation of the intervention, we also aim to ensure that the pilot study provides us with preliminary data to accurately estimate the sample size for a fully-fledged intervention study in the future. That is, we expect the pilot data to enable accurate estimation for the within-group variance, intraclass correlation, and estimate of true effect size for a larger study. Thus, we approach the sample size estimation through a formal but naïve approach assuming there are two groups to compare (instead of three, and not accounting for multiplicity). We consider (re)enrolment in school or vocational training as the primary outcome. The sample size is estimated using the following parameters: in the lived experiences survey implemented in Malawi, the proportion of pregnant or parenting adolescents who were currently out of school was 94%. In a study conducted by the Population Council in Kenya, the proportion of adolescent mothers re-entering school following an intervention comprising policy dialogue, values clarification, and advocacy ranged from 10 to 16% [32]. Given that our proposed intervention addresses the key barriers to school re-entry identified in the Population Council study, we expect a higher rate of re-entry. For this study, we shall assume that the intervention, at the minimum, will achieve a 15% absolute reduction in the proportion of adolescents not in school. The minimum total required sample size for detecting this difference between two groups for a two-sided level of significance of 10%, and statistical power of 80%, can be computed as:$$n=\frac{{[{Z}_{1-\frac{\alpha }{2}}\sqrt{2\overline{pq} }+{Z}_{1-\beta }\sqrt{{p}_{1}\left(1-{p}_{1}\right)+{p}_{2}\left(1-{p}_{2}\right)}]}^{2}}{{({p}_{1}-{p}_{2})}^{2}}$$$${p}_{1}$$ is the proportion of pregnant or parenting adolescents who will be out of school in the intervention groups; $${p}_{2}$$ is the proportion for the arm receiving only the mothers club.; $$n$$ is minimum sample size per arm;$$\overline{p }=\frac{{p}_{1}+{p}_{2}}{2}$$, and$$\overline{q }=1-\overline{p }$$. Assuming a refusal or non-consent or attrition rate of 15% and a design effect of 1.1 due to possible clustering of adolescents from the same enumeration area (EA), the required sample size for detecting a difference between the control arm (group receiving only mother club membership) and one intervention arm is 90 adolescents per arm. In this pilot study with three arms, a total sample size of 270 adolescent mothers is needed.

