### Potential study limitations

While we will adopt a rigorous study design, there are several potential limitations of the study. First, although the selection of the interventions was informed by findings from surveys of pregnant and parenting adolescent girls in Burkina Faso and Malawi and dialogues with community members and other stakeholders, including adolescent mothers, these interventions may be perceived to have been selected in a top-down rather than participatory approach. Second, the one-year duration of the RCT may be too short to observe any effects particularly if there are restrictions on when adolescent mothers can (re)enroll in school or vocational training programs. Finally, there may be differential attrition by study arm between baseline and endline that may limit our ability to draw conclusive evidence on the effects of the interventions.

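### Covariate adjustment is said to account for differential attrition, but it does so only where the listed covariates explain the loss; nothing stated covers loss that depends on enrolment

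*Protocol article*

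**What the plan says.** Under Data processing and analysis, the article plans an intent-to-treat comparison, makes the primary analyses unadjusted, and then states: "We will also compute adjusted effects (controlling for covariates) to account for differential attrition or any differences at baseline". The Covariates section lists age, socio-economic status, family and living circumstances, marital and employment status, and neighbourhood assets. Baseline enrolment and intention to return are not on the list, although the Primary outcome section says both are asked at baseline.

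The same section takes the primary outcome from a question put to participants at endline about attendance since baseline. Potential study limitations concedes that "there may be differential attrition by study arm between baseline and endline" and that this could weaken the conclusions.

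Three other places bear on who is likely to be lost:
- Conditional cash transfers: arm-three payments depend on enrolment, and field staff visit schools to confirm it.
- Adolescent mothers' clubs: in all arms, health workers record attendance at fortnightly sessions and follow up mothers who miss them.
- Process evaluation (Targeted population and approach): administrative data will cover costs, club attendance and childcare use, "as well as adolescent mothers’ enrolment in school and vocational training". The day-care and school registries are named as sources.

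**The concern.** The article names a remedy for attrition and gives its purpose, and the purpose goes beyond what the method can deliver. Regression on baseline covariates corrects for loss only when, within arm and covariate pattern, lost and retained mothers have the same chance of having enrolled. If being found at endline depends on enrolment itself, adjusting for age, family structure or marital status leaves most of the bias in place.

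That mechanism is plausible here. An arm-three mother who enrols gains a school-visit and payment link that one who does not enrol lacks. The link arises after baseline and from the outcome, so no listed covariate captures it.

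Two uses of the result are at stake. Sample size and sample selection wants the pilot to inform the effect size for a larger trial, and cost per (re)enrolled mother is the main cost-effectiveness measure. A biased enrolment difference would carry into both.

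**Working it through.** **Inputs from the article (Sample size and sample selection).** Out of school in the clubs-only arm 94%, so 6% enrolled. The intervention "will achieve a 15% absolute reduction in the proportion of adolescents not in school", read as 94% to 79%, so 21% enrolled. Two-sided 10% significance, 80% power. "Assuming a refusal or non-consent or attrition rate of 15% and a design effect of 1.1". The stated result "and one intervention arm is 90 adolescents per arm".

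**The plan's own figure.** With the printed formula, mean p = 0.865 and mean q = 0.135:

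n = [1.645 × √(2 × 0.865 × 0.135) + 0.842 × √(0.79 × 0.21 + 0.94 × 0.06)]² / 0.15² = 63.1, so 64 per arm.

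64 × 1.1 = 70.4, and 70.4 / 0.85 = 83, against the stated 90. Reading the 15% as relative (94% to 79.9%) gives n = 70, then 77.0, then 91. The difference from 90 is conservative and has no bearing on this point.

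**Assumptions.** The article gives only one 15% allowance, combining refusal, non-consent and attrition. All arm- and outcome-specific loss rates below are assumed.

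**Bias of the unadjusted difference.** With true enrolment p, loss L1 among enrolled and L0 among non-enrolled mothers:

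observed rate = p(1 − L1) / [p(1 − L1) + (1 − p)(1 − L0)]

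The true difference is 21% − 6% = 15.0 points.

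| Loss, enrolled / not enrolled | Arm three observed | Clubs-only observed | Difference | Bias |
|---|---|---|---|---|
| 4% / 18% in arm three; unrelated to enrolment in clubs-only | 0.2016 / 0.8494 = 23.7% | 6.0% | 17.7 | +2.7 |
| 4% / 18% in both arms | 23.7% | 0.0576 / 0.8284 = 7.0% | 16.8 | +1.8 |
| 5% / 17.8% in arm three only | 0.1995 / 0.8489 = 23.5% | 6.0% | 17.5 | +2.5 |
| 5% / 25% in arm three only | 0.1995 / 0.7920 = 25.2% | 6.0% | 19.2 | +4.2 |
| 5% / 17.8% in clubs-only arm only | 21.0% | 0.0570 / 0.8297 = 6.9% | 14.1 | −0.9 |

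Overall arm-three loss is 15.1%, 15.1%, 15.1% and 20.8% in the first four rows. With no true effect and the same pattern in both arms, the bias is zero. With 6% enrolment in both arms and 5% / 17.8% loss in arm three only, it is +0.9.

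**Does adjustment help?** A simulation of 1,000,000 records used one standardised baseline covariate (log-odds coefficient 0.8 for enrolment) and compared the unadjusted difference with a covariate-adjusted logistic estimate standardised to the full sample:

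| Loss mechanism | Unadjusted | Adjusted | True |
|---|---|---|---|
| 5% / 17.8% by enrolment, arm three | 17.6 | 17.3 | 15.0 |
| 5% / 25% by enrolment, arm three | 19.2 | 18.8 | 15.0 |
| By the measured covariate, opposite directions by arm | 16.9 | 15.1 | 15.0 |

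In the first two rows adjustment removes about 0.2 and 0.4 of a point from biases of 2.6 and 4.2 (the 17.6 differs from 17.5 above through simulation error). In the third it removes nearly all of 1.9.

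**Scale.** With 90 × 0.85 = 76.5 retained per arm, the standard error is √[1.1 × (0.21 × 0.79 + 0.06 × 0.94) / 76.5] = 5.7 points. A bias of 2 to 4 points is roughly a third to three quarters of that.

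**Range for lost mothers.** For an observed 15-point difference with 15% missing per arm:
- Extreme cases: 0.1785 − (0.051 + 0.15) = −2.3 points, to (0.1785 + 0.15) − 0.051 = +27.8 points.
- 6% enrolled among lost arm-three mothers and 20% among lost clubs-only mothers: (0.1785 + 0.009) − (0.051 + 0.03) = 10.7 points.
- 40% and 6%: (0.1785 + 0.06) − (0.051 + 0.009) = 17.9 points.

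**The case against.** The strongest reply is that adjustment is a legitimate secondary analysis when measured covariates explain the loss, as the third simulated case shows, and that imputation, weighting and bounds belong in an analysis plan that is not shown. The second part is a fair reason not to fault the article for lacking a missing-data section. It does not rescue the sentence itself, which states a method together with a purpose that the method meets only under an unstated condition.

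Four stronger readings are tempting, and the article does not support them.
- That the primary analysis is wholly unprotected, or biased as it stands. It is unbiased if loss is unrelated to enrolment within each arm. That it rests on re-interviewed mothers is also an inference, from the endline question and the attrition allowance; the article does not define the analysed set.
- That the article expects attrition to differ by arm. It says only that it may, and discloses this as a limitation.
- That the bias will favour arm three. Club contact does not depend on enrolment and may weaken the mechanism, and no retention figures are given. Stronger enrolment-dependent loss in the clubs-only arm would push the other way.
- That registers should simply supply the primary outcome for lost mothers. This would mix self-report with records and could code mothers who moved as not enrolled. Coverage of training centres is not established.

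The objection that weighting or imputation also assumes measured data explain the loss stands. It is why sensitivity analyses are needed alongside them.

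**Conclusion.** The point holds as a stated remedy with an overstated purpose. Adjustment for the listed covariates accounts for differential attrition only when loss is unrelated to enrolment given arm and those covariates, and two obvious predictors, baseline enrolment and intention to return, are not among them. The unadjusted primary analysis has no stated protection if loss depends on enrolment.

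At the planned 15-point effect, assumed patterns with loss heavier among non-enrolled arm-three mothers give a bias of about 2 to 4 points, of which adjustment removes roughly a tenth in the simulated cases. These sizes rest on assumed loss rates and one assumed covariate strength. The bias is smaller where few mothers enrol and vanishes at the null if the same loss pattern applies in both arms. Its direction is not established. It falls short of one standard error in a declared pilot, so the estimate should be better supported, but the design is not undermined.

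**What to change.** In Data processing and analysis:
1. Keep the unadjusted analysis as primary.
2. Reword the adjustment sentence so that it addresses baseline imbalance and only such attrition as the covariates explain.
3. For attrition, specify inverse-probability weighting or multiple imputation by arm, using baseline enrolment, intention to return, the listed covariates and club attendance, with voucher use added in arms two and three only. Club attendance is post-baseline, so it belongs in the weighting or imputation model and not as a covariate in the effect model.
4. Add sensitivity analyses: extreme-case bounds or, more informatively, a stated range of enrolment among lost mothers in each arm; and a register-based outcome for lost mothers, provided registers are checked the same way in all arms.

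The cost is modest extra analysis, largely with data already planned. The extreme bounds will be wide, about −2 to +28 points at 15% loss. Register coverage will be incomplete for training centres and for mothers who moved, which is why that analysis should remain a sensitivity analysis.
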